#### Identification of general practice consulters

Electronic records of participating general practices will be screened to identify adults aged 45 years and over who have consulted for knee pain in the last 24 months, using knee pain related diagnostic or symptomatic Read/Systematized Nomenclature of Medicine (SNOMED) codes. General practice staff will also identify potentially suitable participants during prospective consultations. In the event of slower than expected recruitment, we will increase the number of participating general practices and increase the time period for previous consultation with knee pain from 24 to 36 months.

#### Screen of physiotherapy referrals

Physiotherapy referrals will be screened to identify adults aged 45 years and over with knee pain potentially due to OA.

#### Self-referral from the community

Not all individuals with knee OA will consult healthcare about their knee problem. Information about the trial will be disseminated in the local communities around the participating sites via an awareness raising campaign. Interested participants will telephone the trial administrator to register their interest.

### Screening

Identified individuals will be mailed a covering letter and Participant Information Leaflet (PIL). If interested in participating they will be asked to telephone the trial team: a trial administrator will check initial eligibility and answer any questions. Individuals who fulfil telephone eligibility criteria and are willing to participate will be invited to attend further face-to-face screening (Clinical Eligibility Assessment). At this visit activities will include:

#### Confirmation of eligibility assessment by a PROP OA-trained physiotherapist

A clinical examination will be undertaken to confirm eligibility and to determine, on clinical grounds, the predominant knee compartment affected (medial tibiofemoral, lateral tibiofemoral, patellofemoral, no clear predominant compartment).

#### Plain X-rays of knees (if needed)

To minimise unnecessary radiation exposure, we will attempt to access and read any knee X-rays taken within 24 months where they exist. We will obtain new knee X-rays for eligible participants who have no knee X-rays within 24 months, or whose knee X-rays are unobtainable/unsuitable (eg, poor-quality images, lack necessary views). All images will be taken in the radiology departments at each site using National Health Service (NHS) standard protocols. The treating physiotherapist will assess the X-rays for the purpose of producing an overall judgement on the most severely affected compartment.

After 2 weeks (to allow reporting of X-rays), eligible participants willing to participate in the trial will attend a ‘Treatment Visit’ where informed consent will be obtained (by a trial physiotherapist), baseline data collected, randomisation performed and trial treatments provided.

### Allocation

Using Keele Clinical Trial Units (CTUs) computerised web-based randomisation service and random number generator, eligible participants recruited to the trial will be randomly assigned to receive either advice, written information and exercise instruction alone or advice, written information, and exercise instruction plus knee brace, using a 1:1 allocation ratio and random permuted blocks. This is a secure randomisation system with emergency telephone back-up. Randomisation will be stratified by physiotherapy clinic site (Cheshire, Manchester, Northumbria and Staffordshire), predominant compartmental distribution of knee OA based on combination of clinical assessment and X-rays, and by presence of instability (buckling). Randomisation will be executed in real time within the Treatment Visit by a clinic administrator. The randomisation code will be allocated only after the participant has been recruited into the trial, and after all baseline data are collected. The randomisation schedule will be password protected to ensure that allocation remains concealed from all staff involved in the randomisation process. Thus our procedures ensure baseline data are collected prior to randomisation, that the allocation is concealed until after the participant has been recruited into the trial and until the moment of randomisation and that the person assigning participants to intervention arm (clinic administrator) has no involvement in the eligibility screen, consent or treatment processes.

### Blinding

Within this trial it is impossible to blind participants or physiotherapists to treatment allocation. However, a trial administrator will oversee collection of baseline questionnaire data ahead of treatment allocation and a trial administrator will remain blind to treatment allocation to enable them to conduct Minimum Data Collection (MDC) over the telephone free of allocation bias. The trial statistician who will be performing analysis of the data collected will also be blind to treatment allocation.

### Interventions

#### Comparator: advice, written information and exercise instruction

A single, face-to-face, 20 min consultation with a physiotherapist that, in line with NICE core treatment recommendations for OA,^10^ will include: verbal and written education regarding pathogenesis and prognosis of knee OA and the benefits of exercise, increasing physical activity and weight loss; simple self-help advice on pain management, including home-use of heat/cold, pacing of activities and simple analgesia (we will use the Osteoarthritis Guidebook (https://www.keele.ac.uk/media/keeleuniversity/ri/primarycare/pdfs/OA_Guidebook.pdf) with minor trial-specific changes adapted by Public and Patient Involvement and Engagement (PPIE)); and advice to complete a home-based lower limb exercise programme focusing on muscle strengthening, knee range of movement and proprioception (see online supplemental datafile 2). This reflects ‘best care’ routinely available in primary care where knee OA is typically managed. The content of the advice and exercises was informed by our previous knee OA trials testing physiotherapist led OA care.^44 46^

10.1136/bmjopen-2020-048196.supp2Supplementary data

#### Intervention: advice, written information and exercise instruction plus knee brace with adherence enhancing component

An initial 1-hour face-to-face treatment session with a physiotherapist, a 30 min face-to-face follow-up appointment with the physiotherapist 2 weeks later, and motivational prompts to enhance brace adherence sent via SMS text message over 6 months.

#### Initial treatment session

Participants will receive advice, written information and exercise instruction as described above, plus knee brace and adherence enhancing components.

##### Knee brace

In addition to advice, written information and exercise instruction, participants will be given either a patellofemoral, tibiofemoral unloading, or neutral stabilising knee brace according to whether their pattern of knee OA was predominantly patellofemoral OA, tibiofemoral OA (medial/lateral) or generalised knee OA. This will be based on clinical assessment and X-ray findings, but also taking into account current and desired level of physical activity, ability to don/doff brace, willingness to wear the brace type, and immediate symptom response when the brace is tried on and tested in clinic. Braces will be fitted to ensure maximum comfort (eg, hinges contoured, straps adjusted and cut to match participants’ body shape and size). Dose of brace use will be individually tailored. Participants will be advised to wear the brace on painful weight-bearing activity, with a starting minimum usage of 1 hour on ≥2 days/week, gradually increased based on tolerance to wearing the brace on all painful weight-bearing activities up to a maximum of 8–12 hours/day. Individuals will be advised to wear the brace for 6 months and continue to wear it beyond this time if they find it beneficial. Verbal and written information will be provided on brace application and care, including cleaning instructions and what to do in instances of slippage, discomfort or skin irritation. Supporting patient material (eg, written information, short video clips) on brace application produced by the brace manufacturers will be available.

The braces selected for use in this trial are from the two most-referenced manufacturers in the medical literature (Össur and Donjoy)^47^ and the manufacturer of the patellofemoral brace (Bioskin) previously demonstrated to be clinically effective in a similar population as intended with the current trial.^40^ The braces, by type, are: patellofemoral—Bioskin Q Brace; tibiofemoral unloading—Össur Unloader One (first choice), Donjoy OA Nano (second choice); neutral stabilising—Össur Formfit Knee Hinged. These have been selected to provide an appropriate brace within each brace type, based on previous trial experience and evidence, PPIE feedback and expert opinion (including Clinical Advisory Group (CAG) members’ views).

##### Brace adherence enhancing component

Brief motivational interviewing (MI) techniques will be used to build participants’ intrinsic motivation and resolve ambivalence about adhering to brace use.^48^ The techniques will be based on brief strategies to enhance motivation to change,^48^ including both communication strategies and motivational techniques. Communication strategies include: (1) open-ended questions that invite patients to provide their thoughts about brace adherence in a non-judgemental atmosphere, (2) use of affirmations or statements that creates rapport and recognises participants’ strengths and small steps towards improved adherence; (3) reflective listening to convey provider understanding, provide new perspectives on their situation and help providers deal with resistance and (4) use of summaries to help resolve ambivalence and highlight the patient’s self-motivational statements. Motivational techniques include (1) helping the patient weigh the costs and benefits of adherence to brace use, (2) providing education and feedback on adherence using the ‘elicit-provide-elicit’ process, (3) exploring barriers and facilitators of motivation to adhere and confidence to adhere, and (4) discuss how adherence can enhance, rather than detract from, things they most highly value (values clarification). Participants will be provided with a diary which they can use to record whether they have worn the brace, for how long, if not what were the barriers to wearing the brace, and what are the possible solutions to those barriers.

#### Follow-up treatment session

During the follow-up consultation the physiotherapist will check response to, and fit of the brace. For participants who report tolerating it well and finding it helpful, brace use will be increased for longer durations of painful weight bearing activity. If participants are experiencing discomfort or not finding it helpful, brace fit and dose may be reduced. In extreme cases, if the brace is not tolerated, it may be changed. Adherence to brace use will be reviewed and addressed using brief MI techniques and based on information provided within the brace diary.

#### Motivational prompts to enhance brace adherence

Motivational prompts to encourage brace adherence will be sent to individuals receiving advice, written information and exercise instruction plus knee brace intervention via Short Message Service (SMS) text message. The content of these texts will be tailored to the level of brace use reported by the participant (low: wearing knee brace on less than 2 days per week; mid: wearing knee brace on 2–4 days per week for 1 or more hours per day or wearing knee brace on 5–7 days per week for 1–3 hours per day: high: wearing knee brace on 5–7 days per week for 4 or more hours per day). For example, patients who have low use will receive texts that target their ambivalence about wearing the brace; those with moderate levels of use will receive texts about problem solving and barriers along with some motivational strategies and those with the highest level of use will receive congratulatory messages and messages regarding potential benefits they may have incurred. Motivational prompts will be sent weekly for the first 4 weeks, fortnightly for the next 8 weeks, and then monthly until the intervention period ends at 6 months.

### Cointerventions

All participants will be advised that they can continue to access usual healthcare, including medications and consultations with other health professionals. Participants allocated to the comparator arm will be asked not to wear a knee brace for the 6-month period following randomisation. Details of cointerventions will be recorded in follow-up questionnaires.

### Study training

Physiotherapists delivering trial interventions will be representative of the range of physiotherapists that patients would see beyond the trial in the UK NHS setting. Participating physiotherapists will deliver both interventions and will receive a 3-day PROP OA training programme prior to the trial starting, regular reminders regarding the content of treatment sessions for the first 3 months, and refresher training at 6 months and 1 year. Training will cover all trial aspects including: clinical assessment; reading and interpretation of plain knee X-rays to judge compartmental involvement and inform brace allocation; provision of trial interventions, including dovetailing the provision of knee braces with brief MI techniques to facilitate brace adherence and Good Clinical Practice (GCP) and trial procedures. To promote protocol fidelity, the training programme will be delivered using interactive group discussion, problem solving, case examples and role play. In addition, physiotherapists will receive a PROP OA manual to following when delivering both interventions. Physiotherapists will record intervention provision using case report forms (CRFs), which will be monitored over the course of the trial and used to assess ongoing treatment fidelity.

### Outcomes

The end points are defined as: primary end point at 6 months for clinical effectiveness and at 12 months for cost-effectiveness analysis, and withdrawal for any reason. A schedule of enrolment, interventions and assessments is provided in table 2.

**Table 2 T2:** Schedule of enrolment, interventions and assessments

Time point	Enrolment	Random allocation	Post-randomisation			
	−8 to −0 weeks	0	2 weeks	3 months	6 months	12 months
**Enrolment**						
Telephone eligibility assessment	X					
Informed consent to assessment	X					
Clinical eligibility assessment	X					
Knee X-ray acquisition/reporting	X					
Knee X-ray assessment		X				
Informed consent to randomisation, treatment		X				
Random allocation		X				
**Interventions**						
Advice, written information and exercise instruction		X				
Advice, written information and exercise instruction+knee brace		X	X			
**Assessment****						
Demographics	X					
Medical history and physical assessment	X					
Pain manikin	X					
Frequent knee symptoms in last month	X					
KOOS-5*	X			X	X	X
KOOS Activities of Daily Living†	X			X	X	X
KOOS Pain†	X			X	X	X
KOOS Symptoms†	X			X	X	X
KOOS Sports/Recreation†	X			X	X	X
KOOS Quality of Life†	X			X	X	X
KOOS-4	X			X	X	X
Knee pain on weight-bearing activity (0–100 NRS)†	X			X	X	X
Intermittent and Constant Pain (ICOAP)	X			X	X	X
Knee buckling‡	X			X	X	X
Physical activity (IPAQ-E)	X			X	X	X
Arthritis self-efficacy	X			X	X	X
HADS: Anxiety	X					
HADS: Depression	X					
PROMIS Social participation	X			X	X	X
Adverse events			X	X	X	X
Adherence§			X	X	X	X
Patient global rating of change¶				X	X	X
OARSI-OMERACT responder criteria				X	X	X
Treatment acceptability				X		
EuroQol EQ-5D-5L	X				X	X
Healthcare resource use (NHS/private)	X			X	X	X
Out-of-pocket expenses	X				X	X
Time off work	X				X	X

*Primary outcome.

†Key secondary outcomes.

‡Single item used for stratified randomisation, multiple items used for outcome evaluation.

§Obtained in part through: two-way SMS text messages at weeks 1, 2, 3, 4, 6, 8, 10, 12, 16, 20, 24, 52; self-report via questionnaire at 3, 6 and 12 months.

¶Measure used only to classify OMERACT-OARSI responder.

**Close-out at 12 months for analysis of clinical effectiveness.

HADS, Hospital Anxiety and Depression Scale; ICOAP, Intermittent & Constant Osteoarthritis Pain; IPAQ-E, International Physical Activity Questionnaire-Elderly; KOOS, Knee Osteoarthritis Outcomes Score; NHS, National Health Service; NRS, Numerical Rating Scale; OARSI-OMERACT, Osteoarthritis Research Society International; PROMIS, Patient-Reported Outcomes Measurement Information System.

The primary outcome is patient-reported composite knee score of patient reported pain, other symptoms, ADLs, function in sport and recreation and knee-related quality of life (KOOS-5).^49^

#### Secondary endpoints/outcomes

Secondary outcomes include patient reported pain, other symptoms, ADLs, function in sport/recreation and knee-related quality of life (KOOS subscales),^49^ pain (pain on weight-bearing activity (Numerical Rating Scale)), intermittent and constant pain (ICOAP)^50^; instability (buckling)^51^; Osteoarthritis Research Society International responder criteria^52 53^; physical activity (International Physical Activity Questionnaire-Elderly^54^; social participation (PROMIS)^55 56^; arthritis self-efficacy^57^; treatment acceptability^58^; (SAE). KOOS Pain items contain those needed to score Western Ontario and McMaster Universities Osteoarthritis Index (WOMAC) Pain, KOOS ADLs score is the same as WOMAC Physical Function score and KOOS-4 can be easily computed: all of which permits wider comparison of findings and facilitates future individual participant data (IPD) meta-analysis (see table 2).

#### Cost-effectiveness

Outcomes include the EQ-5D-5L questionnaire^59^ and self-reported knee OA-related resource use related to both primary and secondary care consultations, inpatient stays and treatment including surgery. Data will be collected within the trial to determine the cost of the interventions (physiotherapist time, cost of braces). Unit costs from standard UK sources will be sought for all healthcare resource use items. Data on broader costs will also be collected, related to both out of pocket costs (eg, over-the-counter medications), private healthcare and time off work to calculate productivity losses.

#### Time to and receipt of knee surgery (knee arthroscopy and knee joint replacement)

All participants will be invited to consent to linkage of their trial data to the Hospital Episode Statistics and National Joint Registry and medical record review to enable future evaluation of receipt of knee arthroscopy and knee joint replacement.

#### Adherence

Adherence to interventions will be measured via self-report in follow-up questionnaires (using similar questions to those we have used in previous trials of non-pharmacological care for OA).^44^ In those randomised to advice, written information and exercise instruction plus knee brace, SMS text messages will also seek data on number of days per week and hours per day of brace usage, sent on a tapering schedule over the first 6 months of follow-up, with a text message also at 12 months. We will seek to include an objective measure of adherence to brace use, with participants blinded to this.

#### Adverse events

The occurrence of adverse events considered to be related to the trial interventions for each intervention will be monitored and assessed using CRFs, contact with the trial team, physiotherapist report and follow-up questionnaires. Expected adverse events from knee braces for knee OA include: swelling, blisters and skin irritation. An expected adverse event from unaccustomed exercise and physical activity is temporary, mild muscle soreness. An SAE is an untoward event that: (1) results in death; (2) is life threatening; (3) requires hospitalisation or prolongation of existing hospitalisation; (4) results in persistent or significant disability/incapacity; (5) consists of a congenital anomaly/birth defect or (6) is otherwise considered medically significant. Where an SAE is considered to be potentially related to trial procedures, reporting procedures will be followed that are in accordance with GCP guidance. All SAEs either confirmed or suspected to be related to the trial procedures will be considered by the external monitoring committees.

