Exploratory subgroup analyses will be performed (if numbers in each subgroup are sufficient for these analyses to be feasible) based on the presence of knee instability (buckling), predominant knee compartment involved, level of adherence and anxiety/depression. Participants will also be included in a per-protocol analysis if they meet prespecified inclusion criteria, defined fully in the a priori analysis plan. Cross-tabulation and the kappa statistic will be used to test how accurate brace allocation would have been if based on clinical judgement alone, rather than on clinical assessment findings and X-ray assessment combined. Treatment acceptability will be described using numbers and percentages. Any adverse events and protocol violations will be reported throughout the trial by intervention arm. No interim analysis will be undertaken during the trial to assess the clinical effectiveness of advice, written information and exercise instruction plus knee bracing over advice, written information and exercise instruction alone, however, an internal pilot trial phase will be conducted with prespecified progression criteria (online supplemental datafile 1).

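### A 2-week adverse event assessment is scheduled for both arms but only the brace arm has a described 2-week contact, so by-arm counts are open to an early detection imbalance

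*Protocol article*

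**What the plan says.** Four parts of the protocol article bear on this.

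- **Schedule.** The adverse event row of Table 2 reads "Adverse events X X X X". The marks stand at 2 weeks, 3, 6 and 12 months, and no footnote limits the row to one arm.
- **Sources and scope.** The Adverse events section covers "The occurrence of adverse events considered to be related to the trial interventions for each intervention" and says that these "will be monitored and assessed using CRFs, contact with the trial team, physiotherapist report and follow-up questionnaires".
- **Contacts.** The comparator is "A single, face-to-face, 20 min consultation with a physiotherapist". The brace arm has a longer first session and then "a 30 min face-to-face follow-up appointment with the physiotherapist 2 weeks later". The Follow-up treatment session section adds: "During the follow-up consultation the physiotherapist will check response to, and fit of the brace". Under Data collection, both arms receive posted questionnaires at 3, 6 and 12 months.
- **Reporting.** Statistical methods states: "Any adverse events and protocol violations will be reported throughout the trial by intervention arm".

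**The concern.** A by-arm table of adverse events is read as a comparison, whether or not a test goes with it. That reading is fair only if both arms had the same chance of having an event recorded. Here one arm sees a physiotherapist face to face two weeks after treatment starts, at a scheduled adverse event assessment, and physiotherapist report and CRFs are named sources. The other arm must recall the same kind of event on a form posted at 3 months. Mild, short-lived problems are the ones most easily lost over that interval.

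Safety of bracing is a stated secondary objective. If the sources are pooled, the table could show more events with the brace where no true difference exists, and a reader could not tell how much of the excess comes from the extra visit.

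A second, smaller matter is scope. One section confines monitoring to events thought to be related to the interventions, and another promises any adverse events. These two rules give different tables.

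**Working it through.** **Is there a figure to reproduce?** No. The article gives no adverse event rate, capture rate or precision target for safety. The check is a count of occasions, followed by an illustration on assumed values.

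**Step 1: occasions described after the treatment session**

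| Time | Brace arm | Comparator arm |
|---|---|---|
| 2 weeks | Physiotherapist visit | None described |
| 3 months | Posted questionnaire | Posted questionnaire |
| 6 months | Posted questionnaire | Posted questionnaire |
| 12 months | Posted questionnaire | Posted questionnaire |
| Total | 4 | 3 |

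The interventions block of Table 2 agrees: a 2-week mark appears for the brace arm only. So the adverse event row asks for a 2-week assessment in everyone, while the text gives no means of making it in the comparator arm.

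**Step 2: direction.** Let r be the true risk, equal in both arms. Let c be the probability that the questionnaires capture an event. Let v be the share of events missed by the questionnaires that the 2-week visit picks up.

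- Recorded risk, comparator: r × c
- Recorded risk, brace: r × [1 − (1 − c)(1 − v)]
- Spurious risk ratio: [1 − (1 − c)(1 − v)] / c = 1 + v(1 − c)/c

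The true risk cancels. The ratio is above 1 whenever c is below 1 and v is above 0, so the extra visit can only push towards more recorded events in the brace arm.

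**Step 3: illustration.** The values of r, c and v are all assumed; none comes from the document. Only the arm size does: 434 randomised 1:1, so 434/2 = 217 per arm. With r = 10%:

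| c | v | Comparator | Brace | Risk ratio | Expected events, comparator v brace |
|---|---|---|---|---|---|
| 0.9 | 0.25 | 9.0% | 9.25% | 1.03 | 19.5 v 20.1 |
| 0.7 | 0.50 | 7.0% | 8.5% | 1.21 | 15.2 v 18.4 |
| 0.5 | 0.80 | 5.0% | 9.0% | 1.80 | 10.9 v 19.5 |

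Worked for the middle row: 1 − 0.3 × 0.5 = 0.85, and 0.85/0.7 = 1.21.

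A 2-week visit can detect only what has happened by 2 weeks. A high v is therefore plausible only for early events. Over all events in 12 months v would be lower, and the ratio nearer 1.

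**Step 4: which events.** The article lists swelling, blisters and skin irritation as expected from braces, and mild muscle soreness as expected from exercise. Both arms receive exercise instruction, so soreness can occur in either, and so can knee swelling. Skin problems caused by the brace have no real counterpart in the comparator arm, so unequal detection distorts no comparison there. Serious events are less likely to be missed by a questionnaire and so are less affected.

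**The case against.** The strongest reply is that no formal safety comparison is planned. The objective is the safety of bracing, listed apart from the superiority objectives, and the analysis is reporting by arm with no test. Identical questionnaires cover both arms at three time points, and closer observation of brace wearers serves the stated objective. This is right as far as it goes. It limits the point to counts that are open to imbalance; the document does not show that they are biased. It does not remove the point, because the counts will be set side by side.

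It can also be said that this is an edited version of a fuller protocol and that a separate analysis plan is promised. Either may explain how the 2-week row works in the comparator arm. That may be so, but the schedule and contacts printed here do not agree as they stand.

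Three stronger readings are tempting, and the document does not support them.

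- **That the brace arm's text messages are a further adverse event channel.** They ask about days and hours of brace use, and they are not among the listed adverse event sources.
- **That unblinded staff decide which events count as related.** Participants and physiotherapists cannot be blinded, but the article does not say who judges relatedness.
- **That the monitoring committees see only events already judged related.** The article says "All SAEs either confirmed or suspected to be related to the trial procedures will be considered by the external monitoring committees", which does not exclude others. Under Trial organisation, the data monitoring committee reviews safety, with reports covering interim safety about every 6 months.

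Nor does the article say that CRFs or physiotherapist reports after the first session can come only from the brace arm. It simply describes no later trial session at which a comparator participant would generate one.

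**Conclusion.** The point holds in limited form. As written, the article describes four adverse event occasions in the brace arm and three in the comparator, and the extra one is a face-to-face visit feeding a named source. By-arm counts are therefore open to an early detection imbalance towards more recorded events in the brace arm, mainly for mild events possible in both arms.

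The size is unknown. The range of 1.03 to 1.80 rests wholly on assumed capture rates, and its upper end applies only to events that occur before the 2-week visit. The primary outcome and the sample size are untouched. The difference in scope between related events and any adverse events is a plain inconsistency and needs one wording.

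**What to change.** 1. Build the between-arm adverse event table from the 3-, 6- and 12-month questionnaires that both arms receive, giving the number of respondents in each arm at each time.
2. List events first recorded at the 2-week visit or by physiotherapist report in a separate table, labelled as brace-arm data without a comparison.
3. As an alternative to 1 and 2, make the same 2-week adverse event enquiry in both arms by the same route, which brings the scheduled occasions to four and four.
4. State how the 2-week row of Table 2 applies to the comparator arm.
5. Choose one scope, related events or any adverse events, and use it in both the Adverse events and Statistical methods sections.

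Steps 1, 2, 4 and 5 need only wording and tabulation. The downside is that some early minor brace events fall outside the comparative table and appear only in the brace-arm one. The questionnaires' adverse event wording is not shown, so the common table can be no broader than what they ask. Step 3 costs one more contact for each comparator participant, up to 217.
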